**Sample Selection**

In each of the 4 districts in the evaluation, rural blocks were selected for the evaluation surveys. In UP state, the intervention district of Barabanki has 16 blocks, and CARE worked in 14 of the 16 blocks in the district, all of which were rural. The evaluation study is planned for the 10 blocks where CARE has been able to start their replication strategy immediately as the other 4 blocks has too many sector supervisor vacancies. The comparison district of Unnao has 16 blocks also, 15 of which are rural. Nine blocks will be randomly selected to represent this district in the evaluation. In AP state, each district selected for the evaluation has 15 blocks. In the intervention district of Karimnagar, CARE works in 9 of the 15 blocks, and the evaluation will be conducted in these 9 CARE blocks. In the comparison district of Rangareddy, 8 blocks will be selected randomly for the purpose of this evaluation.

Each block contains 3-6 sectors, an area with 15-25 AWC and an estimated population of 20,000-25,000 persons. In the intervention districts in each state, the sampling universe for survey sample selection include only those sectors and AWC areas that were participating in CARE’s INHP-II program as replication sites. All sectors in the selected blocks will have AWC areas participating in the intervention. In the comparison districts, the sampling universe included all functioning AWC from all sectors of the selected blocks in the district.

Baseline survey

We will use multi-stage survey sampling design to achieve the targeted sample of children and women.

*Uttar Pradesh.* In the intervention district (Barabanki), 2 sectors will be randomly sampled from each block (n=20 sectors). In the comparison district (Unnao), 2-4 sectors will be randomly sampled per block in proportion to the number of AWC per block (n=20 sectors). In both districts, 3 AWC areas will be randomly sampled from each selected sector (n=60 AWC). All the women identified will be interviewed from the sampled AWC areas.

*Andhra Pradesh.* In both districts, 2-3 sectors per block will be sampled in proportion to the number of AWC per block (n=20 sectors), and 4-6 AWC areas will be randomly sampled per sector (n=110 AWC). All the women identified will be interviewed from the sampled AWC areas.

Endline survey

The same sample selection process used at baseline will be employed again at endline.

Adequacy surveys

In all districts, one sector will be randomly sampled from each block for selection of the Adequacy Survey sample. In AP districts, 2-3 AWC per sector will be sampled in proportion to the number of AWC per block for a total of 24 selected AWC areas. In UP districts, 1-2 AWC per sector will be sampled in the same manner for a total of 13 selected AWC areas. The same sample of AWC areas will be used for both adequacy survey rounds to allow for tracking of program exposures in the same AWCs over time.

**Study Instruments**

The study will include three separate instruments:

1. Sociodemographic Questionnaire: This questionnaire will be administered to pregnant women and mothers of children 0-23 months. It will collect data on the respondents sociodemographic characteristics including pregnancy history, age, education, religion, caste, parity, birth intervals, occupation, work history, land ownership, source of income, and basic household amenities.
2. Currently Pregnant Women’s (CPW) questionnaire: This questionnaire will be administered only to women who were pregnant at the time of survey. It will collect information on a wide variety of issues including antenatal care utilization, health behaviors during pregnancy, micronutrient supplementation, dietary intake and practices, rest and workload, and nutritional status.
3. Mothers’ (MOM) questionnaire: This questionnaire will be administered to women with children 0-23 months of age. It will collect information on similar topics as those covered in the pregnant women’s questionnaire. In addition, it will include questions on delivery, postpartum contacts with service providers, infant and child feeding practices and dietary intake, immunization, micronutrient supplementation, and maternal and child nutritional status.

**Data Collection**

The evaluation involve 4 rounds of cross-sectional survey data collection: the baseline survey in January-February 2004, the Adequacy I survey in January 2005, the Adequacy II survey in July-August 2005, and the endline survey in January-March 2006. At each survey round, we will conduct interviews with currently pregnant women and mothers of children 0-23 months of age. Anthropometric measures of weight and height/length will be obtained at the baseline and endline surveys. Hemoglobin measurement for assessment of anemia will be carried out among currently pregnant women and children 12-23 months of age at the baseline and endline surveys only. The surveys will be implemented by TNS with guidance from Johns Hopkins and CARE India investigators.

House listing

A hired survey research firm will conduct a household listing operation in all the sampled AWC areas selected for the samples at each survey round. The purpose of the household listing is to identify households with eligible women and children only. If more than one pregnant woman or mother of a child 0-23 months of age will be identified in a household, interviewers will select one eligible woman randomly from that household. The sample of AWC areas are selected with the expectation of identifying at least 2,400 mothers of children 0-23 months of age and 800 currently pregnant women in each district. For the adequacy surveys, the sample targets will be 500 mothers of children 0-23 months of age and 100 currently pregnant women. However, all eligible women from sampled AWC areas will be recruited for survey enrollment.

Training and field work

Training of interviewers and supervisors for each survey round will be carried out by TNS with on-site technical guidance from JHU, KGMU and CARE personnel. The interview teams will be of 4 interviewers, 1 supervisor and 1 field editor each. There will be six teams per state. The supervisors will be trained to take the weight and height/length measurements from women and children, and to collect a fingerprick blood sample for hemoglobin assessment. The interviewers and field editors will be trained to assist in both these tasks. The JHU field office in Lucknow will organize, train, and manage independent quality control teams to supervise the TNS interview teams and assure data quality. The surveys in Uttar Pradesh and Andhra Pradesh will be conducted simultaneously at all survey rounds.

# Component 2: Data Collection Methods for the Cohort Study

**Population**

A longitudinal design will be employed to assess the program effectiveness as well as specific programmatic exposure that evolves over time in Barabanki and Unnao districts of UP state only. Women in their third trimester of pregnancy will be identified and they will be followed from the time of delivery till the time their baby reaches 18 months of age or the study ends whichever comes first. In each intervention and comparison districts, three rural blocks will be purposively selected.

**Sample Size**

The targeted cohort sample size is 400 eligible women in each arm. Babies born to mothers in this cohort will be followed up until they are 18 months of age. Sample size calculations for the cohort study are presented in table 4.

Here the sample size is calculated to detect differences in dietary intakes between the intervention group and the control group. Assumptions in making these calculations included a power of 80% and a significance level of 95% (alpha = 0.05).

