**Table 4.1 Sample size calculations for cohort study**

| Outcome Measure | SD or P0 | Detectable difference in means by intervention arm | Sample size  per intervention arm |
| --- | --- | --- | --- |
| Dietary intakes  Children  7 - 10 months  11 - 14 months | 200  200 | 75  85 | 150  150 |

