**Data Collection**

As stated earlier, the purpose of the cohort study is to provide information on the course/experience of a sub-sample of potential beneficiaries in UP from the time of entry into the program until time of exit when their children are 18 months of age (or the project ends).

In the cohort study the woman is followed from late pregnancy to delivery, and she and her child are followed every three months postpartum until 18 months of age. These are the critical periods when service providers are suppose to interact and provide specific advices and services to these mothers. These follow-up visits are timed to reflect changes in program emphasis regarding the mother’s and child’s nutrition. At month-12 and month-18 visits, additional 24-hour dietary recalls will be collected on a 10% sub-sample (approximately 96 mothers) to estimate within-subject variation in dietary intakes. This will enable the ER to detect smaller differences in intake than presented (refer Table 4 for estimates presented).

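### Cohort Table 4.1 does not follow from its stated 80% power and does not describe the planned 400 per arm; the 10% repeat recall is credited with a gain in sensitivity that it barely delivers

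*Protocol*

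**What the plan says.** All references are to the Protocol, Component 2 (cohort study), unless stated.

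- **Sample Size**, on the planned number: "The targeted cohort sample size is 400 eligible women in each arm".
- **Sample Size**, on what the calculation is for: "Here the sample size is calculated to detect differences in dietary intakes between the intervention group and the control group". Its terms are: "Assumptions in making these calculations included a power of 80% and a significance level of 95% (alpha = 0.05".
- **Table 4.1** has one row for 7-10 months and one for 11-14 months. The SD, detectable difference and sample size columns read "200 200 | 75 85 | 150 150", and the last column is headed "Sample size per intervention arm". No unit, loss allowance, design effect or different power is attached to either row.
- **Data Collection**, on the repeat recalls: "At month-12 and month-18 visits, additional 24-hour dietary recalls will be collected on a 10% sub-sample (approximately 96 mothers"). The stated purpose is to estimate within-subject variation. The next sentence, which points back to Table 4, says: "This will enable the ER to detect smaller differences in intake than presented".

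**The concern.** Both rows of Table 4.1 share the same SD and the same number per arm, and the text gives one power and one alpha. A two-mean calculation on those inputs has a single detectable difference, yet the table lists two. Neither is the value that the inputs produce.

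The table is also built on 150 per arm, while the cohort is planned at 400. A reader who takes it as the cohort's sensitivity to dietary change would have the wrong figure.

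The Data Collection sentence then promises something better than the table and attributes it to the repeat recalls. Estimating the within-person variance helps to describe usual intake. It does not by itself shrink the standard error of a difference between arm means. At stake is the stated sensitivity for the outcome that the cohort text names in its sizing paragraph, and a benefit credited to a sub-study that hardly provides it.

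**Working it through.** **Inputs.** SD 200, differences 75 and 85, and 150 per arm come from Table 4.1. Power 80%, alpha 0.05 and the target of 400 per arm come from Sample Size. Sidedness is not stated; two-sided is assumed and one-sided is tried below.

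**Step 1: reproduce the table.** n per arm = 2 × (1.96 + 0.8416)² × 200² / d².

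| d | n per arm at 80% power | stated n | power at 150 per arm |
| --- | --- | --- | --- |
| 75 | 111.6, so 112 | 150 | 90.1% |
| 85 | 86.9, so 87 | 150 | 95.7% |

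The power column uses the standard error 200 × √(2/150) = 23.09. For 75, 75/23.09 − 1.96 = 1.29, which gives 90.1%. For 85, 85/23.09 − 1.96 = 1.72, which gives 95.7%.

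**Step 2: look for a reading that recovers both rows.**

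- 90% power: 75 needs 150, which matches; 85 needs 117, which does not.
- 95% power: 185 and 144.
- One-sided 0.05 at 80% power: 88 and 69.
- 150 read as a two-arm total (75 per arm): detectable difference 91.5.
- Unstated loss: 25% for the first row and 42% for the second.
- Unstated design effect: 1.34 and 1.72.
- Unstated larger SD: 232 and 263.

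No single assumption fits both rows.

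**Step 3: the difference the stated inputs give.** Detectable difference = 2.8016 × 200 × √(2/n).

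- n = 150: 64.7 (64.9 with the t distribution), the same for both age bands.
- n = 400: 39.6.
- n = 340, that is 400 less an assumed 15% loss: 43.0.

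The last two come before clustering by AWC. The documents give no cohort design effect; any value D multiplies these differences by √D. The tabulated 75 and 85 are 75/39.6 = 1.9 and 85/39.6 = 2.1 times the difference detectable at 400 per arm.

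**Step 4: what a repeat in 10% can add.** Let w be the within-person share of total variance. The documents do not give it, so it is assumed and varied. A child with one recall has variance 200². A child with the mean of two has 200² × (1 − w/2). With the best possible weighting, the standard error is multiplied by 1/√(0.9 + 0.1/(1 − w/2)).

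| w | multiplier | 64.7 becomes (n = 150) | 39.6 becomes (n = 400) |
| --- | --- | --- | --- |
| 0.4 | 0.988 | 63.9 | 39.1 |
| 0.8 | 0.968 | 62.6 | 38.4 |
| 1.0 (limit) | 0.953 | 61.7 | 37.8 |

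Simulation at n = 150 per arm with w = 0.25, 0.5 and 0.75 gave multipliers of 0.992, 0.985 and 0.972, against 0.993, 0.984 and 0.971 from the formula. The gain is small because nine children in ten still contribute a single recall.

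The repeats fall at months 12 and 18. None lies in the 7-10 month band, so even this small gain is not available for that row.

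**The case against.** **The two rows may share a rounded-up target.** Table 2.1 takes 772 and 633 to a common 800, so 150 could be a common number adequate for both differences. It is: 150 gives at least 80% power in each row. But Table 2.1 prints the unrounded figures and notes the rounding. Table 4.1 does neither, and it labels the column as the detectable difference at the stated power. The reading makes the error harmless in direction; it does not make the table right.

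**The 400 per arm may rest on Table 4.2.** Its largest entry is 398, for exclusive breastfeeding. The usual two-proportion formula for 0.46 against 0.60 gives 199 per arm, so 398 is reproduced only as a two-arm total (2 × 199). Table 4.2 therefore does not explain 400 per arm, and it would not correct Table 4.1 if it did.

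**The repeat recall does help a little.** This stands. A reader might infer that it cannot lower the detectable difference at all, but Step 4 shows a small reduction, under 5% at the limit. The cohort will also detect smaller differences than the table shows. That is because 400 exceeds 150 and because the table is wrong, so only the attribution fails.

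**Two further readings are tempting and fail.**

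- A reader might take the sub-sample of 96 as a slip for 80, which is 10% of 800. But Sampling Strategy fixes 81 AWCs per district (162 in all), Personnel/Staffing expects 5 to 6 births in each, and Eligibility invites every third-trimester woman identified, with no cap. That gives 810 to 972 mothers, and 10% is 81 to 97, so 96 fits.
- A reader might think the age bands miss the visits. Infant feeding data are scheduled at 9 and 12 months, one visit in each band, and the month-12 repeat lies inside 11-14 months.

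**Conclusion.** The point holds. On its own inputs Table 4.1 should show 112 and 87 per arm for differences of 75 and 85, or a single difference of about 65 at 150 per arm. At the planned 400 per arm the figure is about 40, or 43 if 15% loss is assumed, before clustering. This rests on a two-sided test, equal arms and the normal approximation; the t distribution changes it by a fraction of a unit.

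A reader might infer that the cohort is too small for its dietary outcome. The documents do not support that: 150 exceeds what either difference needs at 80% power, and 400 exceeds it further. The defect is a misstated sensitivity in a conservative direction.

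The claim for the repeat recall is oversold. The reduction in standard error is about 1% to 3% for an assumed within-person share of 40% to 80%, and there is no repeat in the 7-10 month band.

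**What to change.** 1. Restate Table 4.1 at the planned 400 per arm, with one stated power and one detectable difference for both ages: about 40 at 80% power with SD 200. State any loss assumption (15% would give 43) and any AWC design effect, multiplying the difference by its square root. If 150 per arm is kept for a reason, give the reason and show about 65.
2. In the cohort Data Collection section, replace the sentence on smaller differences with one saying that the repeat recalls serve to estimate within-subject variation and usual-intake distributions.

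The sub-sample of 96 and the age bands can stay as they are. The cost is an edit to one table and one sentence; recruitment, visits and measurements do not change.

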**Table 4.1 Sample size calculations for cohort study**

| Outcome Measure | SD or P0 | Detectable difference in means by intervention arm | Sample size  per intervention arm |
| --- | --- | --- | --- |
| Dietary intakes  Children  7 - 10 months  11 - 14 months | 200  200 | 75  85 | 150  150 |

**Table 4.2: Estimated sample size for different outcomes**

| Outcome variables | Proportion in unexposed* | Proportion in exposed | Power (1-β) | Type I error (α) | Sample Size |
| --- | --- | --- | --- | --- | --- |
| Initiation of BF | 0.24 | 0.40 | 0.80 | 0.05 | 304 |
| Exclusive BF | 0.46 | 0.60 | 0.80 | 0.05 | 398 |
| Initiation of CF | 0.08 | 0.18 | 0.80 | 0.05 | 354 |
| Weight for age  - 6 mo  - 12 mo  - 18 mo | 0.33  0.28  0.19 | 0.20  0.16  0.09 | 0.80  0.80  0.80 | 0.05  0.05  0.05 | 360  372  376 |
| Height for age  - 6 mo  -12 mo  - 18 mo | 0.19  0.33  0.62 | 0.09  0.20  0.48 | 0.80  0.80  0.80 | 0.05  0.05  0.05 | 376  360  396 |
| Vitamin A | 0.09 | 0.19 | 0.80 | 0.05 | 376 |

** Data source: NFHS-3, Uttar Pradesh, India, 2005-06 report*

**Sampling Strategy**

We got 12.2 pregnant women per AWCs in our baseline survey. Therefore, we estimate that there are approximately 5 (~40%) third trimester pregnant women in each AWC in UP. To enroll 400 3rd trimester pregnant women in each district, we will recruit pregnant women from 81-85 AWCs in each district.

A multi-stage sampling strategy will be employed. In both the Intervention and control districts, 3 blocks each has been selected. The selected blocks are Nindura, Banki and Fatehpur blocks in Barabanki district and Nawabganj, Hasanganj and Asoha blocks in Unnao district. Selection criteria include accessibility from the district town, physical proximity (to the other selected blocks and the town), and the absence of other known large MCH nutrition and health projects (e.g. ICMR). In Barabanki, only blocks where CARE is actively implementing INHP-II replication sites were considered. In Unnao (control district), the comparability of a block's population size and number of AWCs was considered in addition to the other criteria mentioned above. There are 6-7 sectors per block in Barabanki and 5-6 sectors per block in Unnao district. Four sectors will be randomly selected from each of the 3 blocks in each district. Altogether, there are 135 and 192 AWCs in the selected blocks of the intervention and comparison districts respectively. Finally, we selected 6-7 AWCs per sector from both Barabanki and Unnao districts to get the sample size of 81-85 AWCs each for study inclusion.

In Barabanki, we selected 83 AWCs from the list provided by CARE. There were three AWCs where CARE intervention was not in place and hence were dropped. One AWC was further added as it’s name was changed but was a part of our previous CARE list and therefore once name was re-confirmed from the field; was included in the final AWCs list. We finally got a list of 81 AWCs to be included in cohort in Barabanki district.

From the list provided by the District Program Officer (DPO) in Unnao, we selected 84 AWCs. Three AWCs were actually hamlets of other selected AWCs. Therefore, we finally had a list of 81 AWCs in Unnao district also.

**Data Collection**

As stated earlier, the purpose of the cohort study is to provide information on the course/experience of a sub-sample of potential beneficiaries in UP from the time of entry into the program until time of exit when their children are 18 months of age (or the project ends).

In the cohort study the woman is followed from late pregnancy to delivery, and she and her child are followed every three months postpartum until 18 months of age. These are the critical periods when service providers are suppose to interact and provide specific advices and services to these mothers. These follow-up visits are timed to reflect changes in program emphasis regarding the mother’s and child’s nutrition. At month-12 and month-18 visits, additional 24-hour dietary recalls will be collected on a 10% sub-sample (approximately 96 mothers) to estimate within-subject variation in dietary intakes. This will enable the ER to detect smaller differences in intake than presented (refer Table 4 for estimates presented).

***Recruitment***

Eligible pregnant women will be recruited simultaneously at the time of house-listing. One of the team will take oral consent and conduct the interview and take height and weight measurements of the index mother. If there is more than one pregnant women in the household, both will be enrolled for the study. Teams will give one calendar to the respondent (eligible enrolled pregnant woman) with the central office phone numbers to make a call within 24 hours of delivery.

***Eligibility***

All 81 AWCs in both the study districts will be house-listed. Houses will be listed by writing numbers on the right hand of the each front entry/ door of households with a white chalk. Right-hand rule will be followed in listing. According to this rule, when teams will reach a village they well ascertain a central point which is generally the house of the head of the village or sometimes anganwadi centre (AWC). From there, teams will starts numbering (for eg. 99/ NER) the houses moving in the right hand direction. This strategy is employed to avoid missing any household in the village since these rural villages are not planned. Listed households will be enquired about pregnancy status of all the women living in the household. All the women identified in their third trimester of pregnancy will be invited to enroll in the study if they plan to remain in the same household in the immediate future.

***Eligibility criteria***

A comprehensive house-listing will be maintained. All the pregnant women identified for cohort enrollment will be queried to ascertain eligibility.

Women will be considered eligible if:

1. They are at least 24 weeks (completed 6 months/ 180 days) pregnant on the day of house-listing. Gestational age will be assessed by recall of the date of the last menstrual period (LMP) and by asking completed months of pregnancy. In case woman is unsure of her LMP; teams will be provided with local festival calendar that will help in recalling the tentative date of LMP.
2. They intend to remain in the program area (same village) during the duration of the study. Women who are visiting their parents’ home should be excluded unless it is determined that their permanent residence is also within the cohort sample area so they can be followed up at that alternate location. Women who report that they intend to visit their parents’ home for delivery or during the postpartum period can still be enrolled as long as their visit is not intended to be long-term (more than 3 months) and someone in their family is willing to inform our study team about the birth regardless of a woman’s location.
3. Pregnant daughters who are permanently (more than one year) staying with their parents will be considered eligible.

The study will be explained to the women, and if she agrees to participate will be considered eligible. Women will be recruited into the cohort subject to their consent to participate.

